## Abstract

**Background:**

Adolescence is a crucial period for developing and maintaining good habits for mental health and well-being. This is important for future mental health, as most mental health problems manifest during adolescence. Mental health literacy is the foundation for mental health prevention, stigma reduction, and increased help-seeking efficacy particularly among adolescents. The mental health literacy programme “The Guide”, which was developed in Canada, has shown success in increasing mental health literacy in North American 16–17 year olds. “The Guide Cymru” is an adaptation of The Guide designed for a younger age group (13–14 year olds) and for the Welsh culture and context and is being offered to all state schools in Wales.

**Methods:**

This two-armed cluster randomised control trial (RCT) will evaluate the effectiveness of The Guide Cymru. All 205 secondary schools in Wales will be invited to take part, involving up to 30,000 year 9 pupils. Schools will be randomised to either the immediate implementation of The Guide Cymru or to a wait-list control. The wait-list control will receive The Guide Cymru around 12 weeks later. Measures of mental health literacy (assessed via the Knowledge and Attitudes to Mental Health scale) and mental health problems (via the PedsQL and Strengths and Difficulties Questionnaire) will be taken at baseline (pre-intervention), 12 weeks later (after the active group has received The Guide Cymru), and 24 weeks later (after the wait-list control has received The Guide Cymru).

**Discussion:**

The trial aims to evaluate if The Guide Cymru increases mental health literacy, including reduced stigma to others and to the self, and increased levels of good mental health behaviours and help-seeking for mental health problems.

**Trial registration:**

ISRCTN15462041. Registered 03/10/2019.

## Background

Mental health problems are one of the main causes of the burden of disease worldwide [1]. Mental health services in the UK are currently overstretched, individuals experience long waiting times for treatment, and specialist services are often lacking [2]. Despite this, public spending is focused almost entirely on coping with crisis, with little investment in prevention. Specialist Child and Adolescent Mental Health Services in Wales (CAMHS) is under more pressure than ever before as over the past four years they have observed a 100% increase (from 1204 to 2342 cases) in demand use for the service [3].

Most mental health problems manifest in early life, as one in five children worldwide experience mental health problems [4] with 50% of mental health problems evident by the age of 14 [5]. Only 18–34% of young people with high levels of depression or anxiety seek professional help. In a school-based study of 12 to 17-year-old adolescents, only 18.2% with a diagnosable depressive disorder had ever received support from a mental health service [6].

Poor mental health can have significant consequences, on both general health and on behaviour. For example, it is associated with school drop-out and delinquent behaviours [7]. If unrecognised, or untreated, early-onset mental health disorders may lead to substantial negative personal, social and community consequences. Issues such as these underline the need for an early intervention as part of a comprehensive approach to address mental health needs of adolescents. Early detection of a mental health disorder, coupled with early intervention, has led to better health outcomes and more positive attitudes to mental illness and help-seeking behaviours [8].

The stigma attached to mental health can have significant negative impacts on an individual [9]. Mental health stigma can deter individuals from seeking appropriate mental health support. Barney et al. [10] found that both self-stigma (negative thoughts about oneself) and public stigma (negative thoughts about other people) reduced help-seeking attitudes. Self-stigma can also have significant negative impacts on an individual’s self-esteem and self-worth due to an individual labelling themselves as socially unacceptable [11]. Research has consistently found that individuals protect their self-esteem by not asking for help and by avoiding appropriate help-seeking behaviours [12]. This avoidance mechanism also prevents individuals from seeking help from non-professional sources such as family and friends [13].

In order to promote early intervention among adolescents, interventions need to target stigma reduction as the stigma attached to mental health has been shown to prevent help-seeking behaviours among adolescents [14]. Research suggests that enhancing an individual’s mental health literacy can aid stigma reduction through the improvement of public knowledge of mental health and increasing attitudes towards help-seeking behaviours - particularly among adolescents [15]. Mental health literacy originates from the domain of health literacy, which aims to improve patient knowledge about physical health and treatments in order to promote and improve physical health [16]. It has been proposed that mental health literacy programs may play an important role in facilitating access to care among young people with mental health problems.

Mental health literacy has many components, including (a) prevention through good mental health behaviours, (b) symptom recognition, (c) self-help strategies, (d) help-seeking strategies and treatment options, and (e) how to support others in need [17]. This definition of mental health literacy lies among current theories of health promotion, such as stigma theory, which claims that a lack of knowledge is a driver of prejudice (negative attitudes) which, in turn, influences negative behaviour (discrimination) [18]. This model of ignorance leading to discrimination suggests that it is crucial to improve the mental health literacy of adolescents in order to counteract stigmatic-related beliefs about mental health problems.

Many individuals with mental disorders internalise these negative stereotypes about mental disorders, and this negative self-perception has become known as self-stigma. Self-stigma results in harm to self-esteem, self-efficacy, and quality of life [19]. Research has shown that educational programs targeting self-sigma reduction have resulted in higher self-esteem, better quality of life, and increased social support among individuals [20], and improvements in the mental health literacy of adolescents have been shown to be related to increased resilience and control over their own mental health and increases in self-helping behaviour [21].

Currently in the UK there are low levels of mental health literacy in secondary schools [22]. However, educators, health professionals, and policy makers have recognised the importance of schools in being able to address the mental health needs of young people [23]. Hence, a mental health literacy programme that is delivered to all children as part of the school’s curriculum could produce a reduction in mental health related stigma and an increase in help-seeking behaviours for mental health problems, with the hope that this in turn would improve the mental health of these children in the short-term, and as they develop into adults over the long-term.

Action for Children (AfC), a third sector UK charity, have received funding from the Welsh Government to deliver a mental health literacy programme (The Guide Cymru^1^) to all Year 9 pupils (age 13–14) in main stream education throughout Wales. The Guide Cymru is based on an evidence-based intervention and resource aimed at improving knowledge and attitudes towards mental health in adolescent populations [25]. The Guide (Cymru) compromises of six modules including; 1) understanding mental health and mental illness, 2) stigma myths and realities, 3) information on specific mental illnesses, 4) experiences of mental illness, 5) help-seeking and finding support, and 6) the importance of positive mental health. In Canada, the Guide has led to significant improvements in mental health knowledge and stigma in high school student aged 16–17 year olds [25]. The Guide Cymru is based on The Guide but has been revised to be appropriate for a lower age group (12–15 year olds) in order to target the key age of onset of many mental health problems. It has also had its language and terminology revised to fit the culture of the UK/Wales. A Welsh-language version of The Guide Cymru was also produced.

This randomised control trial (RCT) will evaluate the effectiveness of the mental health literacy intervention within a Welsh culture. The Guide Cymru will be delivered to teachers who will then deliver the content to a cohort of all Year 9 pupils (aged between 13 and 14 years) across Wales. While previous evaluations [25] of The Guide have examined knowledge of mental health and attitudes towards mental health, we aimed to take a more detailed assessment that broke this down into knowledge of mental health, good mental health behaviours, stigma to others, stigma to the self, avoidance coping, and help-seeking behaviours.

We hypothesise that children that receive The Guide Cymru will show greater mental health literacy as indicated by: (1) greater knowledge of mental health issues, 2) better mental health related behaviours, (3) less stigma towards those with mental illness, (4) reduced levels of self-stigma, (5) a reduction in avoidant coping styles, (6) a greater intention to seek help if they have a mental health problem.

## Method/design

A CONSORT statement was used to describe the study [26] – see Fig. 1. The study design is a two-armed cluster-randomised wait list control trial of The Guide Cymru mental health literacy programme. The setting is the Year 9 pupils (age 13–14 years) in state schools in Wales.

**Fig. 1 Fig1:**
[figure not shown]
A Consort Representation of Study

A cluster-randomised control trial was deemed necessary as The Guide Cymru training programme is delivered to the students via their teachers and so the school is the unit of clustering. Hence, randomisation will take place at the level of the school and will involve clusters of approximately 150 (range approx. 30–300) students. However, the main outcome (e.g., mental health literacy) will be at the level of the individual students and not at the cluster level.

### Recruitment and consent

All schools in mainstream education in Wales will be sent a letter to their Head-teacher offering free training for up to three teachers on a mental health literacy intervention: The Guide Cymru. This is an evidence-based intervention [25] and resource that can be used as part of the Personal, Social and Health Education curriculum or as part of the Health and Well-being area of Learning and Experience, within each school. Schools that sign-up for the mental health literacy intervention will be stratified by geographical location into groups of around 10 schools. Schools from this group are then randomly allocated to each arm of the trial (The Guide Cymru vs wait list control).

The Guide Cymru is being adopted as part of the National Curriculum and is therefore delivered to all children within the year group at the school and at the teachers’ discretion, without the need for consent from the parents/caregivers. Data collection will be performed in the classroom via pencil and paper questionnaires. Completed questionnaires will contain no personal information to preserve anonymity. However, the participants will be asked four “code” questions that allow for the tracking of the person across the three waves (“name of first pet”, “date of your birth day (e. g,.23^rd^)”, “house number”, and “favourite colour”). Ethical permission for the study has been obtained from Swansea University (Approved 28/10/2018, Department of Psychology Ethics Committee, ref.: 2018–0272-259). Following completion of the Guide Cymru, participating schools will receive general feedback on pupils knowledge, stigma and reported help-seeking behaviours in relation to mental health. No individual pupil data will be reported as only group data will be analysed.

### Randomisation

The randomisation process will take place at the level of schools that wish to be trained on The Guide Cymru (estimated *n* = 120). Schools will be stratified by geographic area. This will help to ensure that the schools in the intervention and wait list control are from similar backgrounds, such as the socio-economic status of the students and their use of the Welsh language, etc.. A computer-generated random sampling procedure will be used to ensure unbiased allocation to each group: (https://www.random.org/). After randomisation, each school allocated to the intervention group will be “yoked” to a school in the wait-list control so that everything that is done to the first school is done to the yoked school in wait list control (e.g., day of testing on each wave of testing). Throughout the study, the randomisation process will be conducted by the acedemic leads of the project, without any influence of the project team.

### Blinding

Schools will be randomised to either the intervention group or the wait list control. After they have signed and returned their Service Level Agreements. Given the nature of the intervention it will be impossible for the schools and students to be blinded as to which arm of the RCT they are in.

### Inclusion/ exclusion criteria

Schools are eligible to participate if:
They are a mainstream state school in Wales.They wish to deliver the intervention as part of their curriculum to Year 9 pupils.They are able to send up to three members of staff to a two-day training programme.

Schools are not eligible to take part if:
If they are a school outside of WalesIf they are a primary school, a special school (for young people with Learning Disability or Behavioural difficulties), or an independent sector school.If they are unable to send at least two teachers to the teacher training programme (see below).They are not to be able to deliver The Guide Cymru intervention following receipt of the training programme.

Young people are eligible if they meet the following criteria:
Aged 13–14, in Year 9 of secondary school, attending a mainstream state school in Wales.Understand written and spoken English or Welsh.

Young people are not eligible to take part if:
They are not currently being educated in a state school in Wales in year 9.

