#### Wave one

The aim of wave one is to provide baseline measures of mental health literacy, and levels of psychological function and mental health difficulties. The wave will occur approximately 1 week prior to these teachers being trained on Go-To Educator and then delivering the intervention programme to their students over the following 10 weeks. A member of our research team will visit each school on the day of testing to help the teachers administer the questionnaires to the students.

For each school in the intervention arm of the RCT there will be a “yoked” school in the wait list control arm and the data from the yoked school will be collected on the same day and in the same manner as the one in the active arm.

We will determine Social Economic Status (SES) and special needs status of the schools through the Welsh Government Annual Documentation detailing a percentage of many pupils are eligible for free school meals and how many require additional learning support.

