#### Wave two

The wave will occur approximately 1–2 weeks post the delivery of The Guide Cymru for the students in the intervention arm of the study, with the wait list control yoked schools being tested at the same time.

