### Challenges and limitations

A major challenge is to be able to deliver the intervention within the time period of the funding. The intervention is delivered over a 8–10 week period (typically) by the schools themselves after the teachers have been trained in the delivery. Hence, the intervention has to be integrated into the curriculum of the schools which are often planned months, if not a complete year, in advance. Hence, while schools might be keen to take advantage of this free resource (funded by Welsh Government), the practical difficulties in assigning teachers to be trained (including inevitable drop-outs, transfers, sickness, etc) and the integration of the intervention programme into the school timetable will limit the number of schools that will be able to deliver the Guide Cymru.

The second limitation is that we will not be able to identify individuals due to the anonymous nature of the data collection. Hence, we will not be able to look at factors such as academic achievement or socioeconomic status as mediating factors in the success/failure of the intervention other than at the level of the school.

Finally, while we will follow students over three phases of data collection that span approximately 6 months. This follow-up period is short compared to the hoped-for benefits of the intervention. We hope that if we are able to show significant benefits within this short-term follow-up then this will encourage further development of mental health literacy programmes along the lines of The Guide and The Guide Cymru. These mental health intertervention programmes within our schools can then become part of the continuing education of students across several years of study, so as to reinforce and consolidate this learning and help young people to develop positive attitudes towards mental health difficulties and help-seeking at times of need, alongside behaviours that promote good mental health.

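### A school exclusion tied to delivery after training can, applied as worded, remove only intervention schools from the primary comparison

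*Protocol article*

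**What the plan says.** The Inclusion/exclusion criteria of the protocol article list four grounds on which a school is ineligible. The last is: "They are not to be able to deliver The Guide Cymru intervention following receipt of the training programme". The one before it concerns schools that cannot send at least two teachers to training.

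The order of events is given elsewhere in the article:

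- **Who is randomised** (Randomisation): "The randomisation process will take place at the level of schools that wish to be trained on The Guide Cymru".
- **When** (Blinding): schools are allocated "After they have signed and returned their Service Level Agreements".
- **Wave 1** (Wave one): "The wave will occur approximately 1 week prior to these teachers being trained on Go-To Educator". Each intervention school already has its yoked wait-list partner by then, and the Randomisation section says that yoking is done after allocation.
- **Wave 2** (Wave two) is timed from delivery: "The wave will occur approximately 1–2 weeks post the delivery of The Guide Cymru for the students in the intervention arm of the study". The Abstract places this wave 12 weeks after baseline.
- **Wait-list arm** (Abstract, Methods): "The wait-list control will receive The Guide Cymru around 12 weeks later".
- **Primary analysis**: a multi-level model comparing waves 1 and 2, with the time-by-group interaction as the effect of interest.

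Under Challenges and limitations, the article adds that practical and timetabling difficulties "will limit the number of schools that will be able to deliver the Guide Cymru".

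**The concern.** An eligibility criterion should rest on facts known before allocation. This one refers to something that happens after training, and training comes after randomisation. Before wave 2, failure to deliver can be seen only in the intervention arm, because the wait-list schools have not yet had their turn. A rule that acts on it would compare selected intervention schools with unselected controls, and randomisation would no longer protect the comparison.

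What is at stake is mainly the meaning and size of the effect. Schools that cannot release staff or find timetable space are part of the setting in which the programme will be used. The article names testing in situ, with ordinary teachers, as a major strength. Leaving out the schools where delivery failed removes part of that picture and makes the programme look more effective than offering it to schools would be.

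**Working it through.** **Order of events.** Putting the sections side by side gives:

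1. Service Level Agreement returned.
2. School randomised, then yoked.
3. Wave 1 in both arms.
4. About 1 week later, intervention teachers are trained; delivery follows over 8–10 weeks.
5. Wave 2 in both arms. The primary comparison is complete here.
6. Wait-list schools receive the programme.
7. Wave 3.

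The exclusion can be judged as worded only from step 4 onwards in the intervention arm and only from step 6 in the wait-list arm. Even if wait-list teachers were trained earlier than the article suggests, their delivery still follows wave 2, so their failures could not be known at the primary comparison.

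**Would dropping the yoked partner restore balance?** No. The pair is formed after allocation, and the partner's own ability to deliver is unknown at wave 2. Removing it does not remove the wait-list schools that would have failed.

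**The plan's own figures** (Statistical power: alpha 0.05, taken as two-sided; power 80%; effect 0.30; cluster size 150; ICC 0.10):

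- Unclustered: 2 × (1.960 + 0.842)² / 0.30² = 174.4, so 175 per group, as stated.
- Design effect: 1 + (150 − 1) × 0.10 = 15.9, rounded to 16, as stated.
- Clustered: 175 × 16 = 2800 per group, N = 5600, as stated.

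These reproduce, and the present point does not alter them.

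**Effect of the exclusion.** Let f be the share of schools that would not deliver, τ the gain in schools that deliver (no gain elsewhere), c the amount by which non-delivering schools score lower at both waves, and g the amount by which they would change less between waves without the programme. In SD units, on the wave 1 to wave 2 change:

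- All schools as randomised: (1 − f) × τ.
- Non-delivering intervention schools removed: τ + f × g.

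The level difference c appears in neither line, because it is present at both waves and cancels. With no true effect (τ = 0), the bias from exclusion is f × g.

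Taking τ = 0.30 from the plan and g = 0, with f assumed because the article gives no rate:

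| f (assumed) | As randomised | Excluding non-deliverers | Overstatement |
|---|---|---|---|
| 5% | 0.30 × 0.95 = 0.285 | 0.30 | 5% |
| 10% | 0.30 × 0.90 = 0.27 | 0.30 | 0.30 / 0.27 − 1 = 11% |
| 20% | 0.30 × 0.80 = 0.24 | 0.30 | 0.30 / 0.24 − 1 = 25% |

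**Can the trial afford the diluted effect?** At 0.24 SD the plan's requirement scales by (0.30 / 0.24)² = 1.5625, giving 2800 × 1.5625 = 4375 per group, or 8750 in all. That is below the predicted 13,000.

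**The case against.** The strongest reply is that the clause may look forward: a school that could not deliver once trained should not sign up. It stands beside entry conditions about wishing to deliver and being able to send staff, allocation waits for a signed agreement, and the article nowhere says that a randomised school is withdrawn or its data discarded. This reading is possible. But nothing confines the rule to sign-up, and its reference to the time after training makes the post-randomisation reading the natural one. If the forward-looking sense was meant, the rewording costs one sentence.

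A second reply is that analysis sets belong in the statistical analysis plan, which is not shown. That is fair for the detail, and its absence is not the point here. Eligibility, however, is fixed in the protocol. An analysis plan that honours this criterion would analyse a selected arm, and one that ignores it would contradict the protocol.

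Some stronger inferences are tempting but not supported:

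- **A reader might infer a large rise in type I error.** That would follow if the outcome were compared at wave 2 alone and non-delivering schools scored lower. The planned test is a time-by-group interaction, in which a stable deficit largely cancels. A rise needs g to differ from zero, and the article gives no value for g or f.
- **A reader might infer that the article predicts failures after randomisation.** The remark on limited delivery may partly describe take-up, since about 205 schools are invited and 120 expected. It makes non-delivery plausible but does not establish a rate.
- **A reader might infer that a non-delivering school has no wave 2.** The Wave two section does time it from delivery, but the Abstract gives a nominal date of 12 weeks.
- **A reader might infer that the two-teacher rule is also judged at training.** The article does not say when it is judged.

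**Conclusion.** The concern holds as a defect in a stated rule. On the article's own timeline, the delivery exclusion applied as worded can act only on intervention schools before the primary comparison, and removing the yoked partner would not repair this. The effect would then be that in delivering schools, not in schools as randomised.

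The size cannot be derived from the article. Under the assumptions that delivering schools gain 0.30 SD and non-delivering schools gain nothing, the reported effect would be 11% too high with 10% non-delivery and 25% too high with 20%. If non-delivering schools gained something from partial delivery, the overstatement would be smaller. No inflation of type I error is claimed beyond the conditional statement that it arises if those schools would change differently between waves without the programme. The conclusion also depends on such schools actually being dropped, which the wording permits but the article does not report as a plan.

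**What to change.** - Reword the delivery criterion as a commitment given on the Service Level Agreement before randomisation. For clarity, do the same for the two-teacher criterion.
- State that every randomised school stays in the primary analysis in its allocated arm, whatever its training attendance or delivery.
- Collect wave 2 at the nominal 12 weeks in every randomised school and its yoked partner, whether or not delivery was completed.
- Report an analysis restricted to delivering schools as supplementary only.

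The cost is a change of wording and questionnaire visits to the few schools that do not deliver. The estimate may be somewhat diluted, but it then answers the in situ question the trial sets itself, and the predicted sample leaves room for that. The change should be made before schools are randomised, because wave 2 data that were never collected cannot be recovered in the analysis.
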